##### Interim-analyses

Interim analyses is planned for the follow-up data collected at 6-weeks post-intervention and will be submitted to Data Safety & Monitoring Board (DSMB) for further review (Table 2).

##### Stopping-rule

The DSMB will be asked to advise stopping the trial if they have proof beyond doubt that intervention is futile. The trial’s stopping-rule will be based on evidence-of-futility in > 70% of outcome measures (both primary &secondary) at interim-analyses and critical feedback from the local stakeholders.

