##### Sample size and power

Positive mental health literacy measured using the 10-item Mental Health-Promoting Knowledge (MHPK-10) scale is considered primary outcome for the present study [26]. However, the Intra-Cluster Correlation for MHPK-10 score is unknown. Based on evidence from similar adolescents studies, we assumed a conservative and modest estimate of ICC (ρ) between 0.01 and 0.05 [34, 35]. From the Kolar District Report (as on 30/3/2016), an estimated average of 50 students is expected from grade-6 and 7 of each higher-primary schools. With a need for 4 schools per arm with 50 students per school, we powered the trial to be able to detect a standardised difference (difference in means/SD) of 0.37–0.56 (medium effect size) for MHPK-10 scores between intervention and control groups for a two-sided level of significance at 5% (*α* = 0.05) with 85% power. For the above assumption, the design effect varied from 1.5 to 3.5 for ICC (ρ) values from 0.01 to 0.05, respectively [36]. We expect a minimum sample size of 400 across 8 schools for 85% power. Even with a 5% loss to follow-up, the study will still have more than 80% power.

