**Trial-Monitoring:** The Project-Assistant will check for intervention-delivery, protocol-adherence, data-collection and reporting using supervisory check-list during their monthly visits. Principal-Investigator will review this monthly visit reports during monthly review meetings. The central-research team (comprising of Principal-Investigator and other expert-collaborators) will have meetings once in 6 months at NIMHANS to review the progress, work plan, discuss and troubleshoot any unresolved field issues. A register will be maintained for all review meetings. Constant support will be obtained from the expert collaborators through tele-meetings. A Trial Steering Committee (TSC) and Data Safety Monitoring Board (DSMB) will be constituted independently of the research team, the members of whom will have no conflict of interest. The TSC will comprise experienced experts to oversee the trial and independently evaluate the trial to monitor progress, intervention delivery, protocol adherence and data management. A three-member DSMB will monitor the data as the trial progresses to identify any emerging safety concerns for the study participants and problems in the study’s conduct. DSMB will decide on the continuation of trial following interim analysis.	
**Intervention Fidelity:** Teachers will be encouraged to fill a protocol-adherence checklist. The educational-intervention delivered by the teacher will be audio-recorded to assess fidelity of intervention delivery. A random sample of audiotaped sessions will be evaluated for each teacher using fidelity checklists for intervention-delivery based on the standardised core content of the SUMS intervention curriculum resource guide. Feedback will be provided to support the booster-training sessions. Our fidelity assessment will also incorporate feedback and recommendations of the independent evaluation and reports of supervisory-checklist.	

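### The 6-week futility rule pools primary and secondary measures in one count, so it can be met while MHPK-10 is clearly positive and missed while MHPK-10 is futile

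*Protocol article*

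**What the plan says.** The timing is in the Interim-analyses section: "Interim analyses is planned for the follow-up data collected at 6-weeks post-intervention", with the results going to the DSMB.

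The criterion is in the Stopping-rule section. The stop "will be based on evidence-of-futility in > 70% of outcome measures (both primary &secondary) at interim-analyses"; the same sentence adds critical feedback from local stakeholders. The sentence before it asks the DSMB to advise stopping only where futility is proven beyond doubt.

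The Trial-Monitoring row of Table 2 describes the DSMB's role differently: "DSMB will decide on the continuation of trial following interim analysis".

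The Sample size and power section sizes the trial on MHPK-10 alone: "With a need for 4 schools per arm with 50 students per school", and "We expect a minimum sample size of 400 across 8 schools for 85% power". It states no power for any secondary measure.

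**The concern.** A percentage taken over primary and secondary measures together gives MHPK-10 the same vote as each secondary scale. No section requires MHPK-10 to be among the futile measures, and none lets a positive MHPK-10 result block a stop. The rule can therefore point the wrong way in two situations. Secondaries for which no power is stated can meet the count while the outcome that sized the trial is positive. Conversely, a futile primary does not meet the count if enough secondaries escape it.

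The look comes before the 6-month and 12-month assessments. A stop taken on this basis would lose both and leave open whether any early benefit lasts.

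**Working it through.** **1. The plan's own design figures.** Inputs from Sample size and power: 4 schools per arm, 50 students each (200 per arm), two-sided 5%, 85% power, and a "conservative and modest estimate of ICC (ρ) between 0.01 and 0.05".

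- Design effect = 1 + (50 − 1) × ICC: 1 + 49 × 0.01 = 1.49, and 1 + 49 × 0.05 = 3.45 (stated 1.5 and 3.5).
- Detectable difference = (1.960 + 1.036) × √(2 × design effect / 200): 2.996 × √0.0149 = 0.366, and 2.996 × √0.0345 = 0.557 (stated 0.37 and 0.56).

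The plan's figures reproduce. They concern MHPK-10 only.

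**2. What meets the count.** The Outcomes section lists one primary (MHPK-10) and seven secondaries: MHLS, the PMHSS personal stigma subscale, RIBS, IASMHS, K6, CD-RISC and the MH-FA vignettes. That makes 8 measures, or 9 if MH-FA knowledge and intentions are counted separately.

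- Of 8: 0.70 × 8 = 5.6, so 6 are needed (6/8 = 75%). Secondaries alone can supply 7/8 = 87.5%.
- Of 9: 0.70 × 9 = 6.3, so 7 are needed (7/9 = 77.8%). Secondaries alone can supply 8/9 = 88.9%.
- In general (N − 1)/N exceeds 0.70 for every N of 4 or more, so the result does not depend on how MH-FA is counted.
- In the other direction, a futile MHPK-10 plus four futile secondaries is 5/8 = 62.5%, which does not meet the count.

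**3. How often the count is met when MHPK-10 is positive.** The article gives no definition of futility, no expected secondary effects and no correlations, so this step is illustrative. Assumptions: 8 measures; correlation 0 to 0.3; 4 + 4 school means with variance ICC + (1 − ICC)/50; t-test on 6 df; true MHPK-10 effect 0.56 SD at ICC 0.05 or 0.37 SD at ICC 0.01. The entries are the percentage of trials meeting the count among those in which MHPK-10 is significant.

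| Meaning of futile | Secondaries 0 SD | Secondaries 0.2 SD, ICC 0.05 | Secondaries 0.2 SD, ICC 0.01 | Secondaries at the design effect |
|---|---|---|---|---|
| No significant benefit at two-sided 5% | 97–99 | 67–72 | 37–38 | under 2 |
| t below 1 | 60–64 | 4–9 | 0.2–1.5 | about 0 |
| Estimate in the wrong direction | 6–13 | at most 0.3 | about 0 | about 0 |

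The null column can be checked by hand at zero correlation, as the chance that at least 6 of 7 secondaries are futile:

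- No significant benefit: 0.975⁷ + 7 × 0.025 × 0.975⁶ = 0.838 + 0.150 = 98.8%.
- t below 1 (probability 0.822 on 6 df): 0.822⁷ + 7 × 0.178 × 0.822⁶ = 0.254 + 0.384 = 63.8%.
- Wrong direction: 8 × 0.5⁷ = 6.25%.

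Under the first meaning, secondary effects of 0.3 SD lower the rate to 38–40% (ICC 0.05) and 4–8% (ICC 0.01). Counting 9 measures changes little: at ICC 0.05 with 0.2 SD secondaries, the share of all trials meeting the count moves from 75–78% to 71–73%.

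**The case against.** The strongest defence is that the count is not the whole rule. It is joined to stakeholder feedback, and the DSMB is asked to advise a stop only on proof beyond doubt. A DSMB applying that standard would hesitate to stop a trial with a clearly positive primary. That stands in part: meeting the count does not end the trial automatically. But neither safeguard mentions MHPK-10, and stakeholder feedback is not a statistical check on the primary outcome.

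A reader might go further and infer that the rule would stop most effective trials, taking non-significance as the natural meaning of futility. The documents do not support that. Non-significance on 6 df is hard to square with proof beyond doubt, and the table shows the rate falling from about 70% to nearly nothing as the definition or the secondary effects change. The definition may also sit in an analysis plan or DSMB charter that is not shown, so its absence from an article is not part of this point. The pooled count is different, because the article itself fixes it.

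A reader might also infer that a stop at 6 weeks would spare almost nothing. That goes too far. The boosters at 2 and 5 months can still lie ahead, two survey rounds remain, and the four waitlist schools have yet to receive teacher training and the whole programme.

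Finally, judging futility across domains has a rationale: the primary objective covers knowledge, attitudes and first-aid behaviours, while MHPK-10 measures only knowledge. That is a reason for the DSMB to see the secondaries. It does not justify letting them outvote the outcome on which the trial is sized.

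**Conclusion.** The point holds as a structural fault in a rule that the article fixes. Six of the seven secondaries (or seven of eight) can meet the futility count with MHPK-10 clearly positive, and a futile MHPK-10 with five futile measures of eight does not meet it. This follows from the count alone and needs no assumption about effects.

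Its frequency is not established. Given a significant primary, the illustrations run from almost none to 97–99%, depending on the meaning of futility, the secondary effects and the correlations, none of which the article gives. The high rates need both a lenient meaning of futility and secondaries that move much less than MHPK-10. The difference between Table 2, where the DSMB decides, and the Stopping-rule section, where it advises, adds uncertainty about how much weight the criterion carries.

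**What to change.** Rewrite the stopping rule so that futility on MHPK-10 is a necessary condition for advising a stop. State it as a non-binding guideline, with its threshold set in advance by the sponsor and the DSMB. A low conditional power for MHPK-10 is one option; it would require naming the time point to which it refers, because the article names no primary one. Secondary outcomes and stakeholder feedback should inform the DSMB's discussion but not trigger a stop. With this condition, the criterion can no longer be met on secondaries alone.

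Reconcile Table 2 with the Stopping-rule section on whether the DSMB decides or advises.

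The cost is about two sentences plus matching DSMB charter wording. The downside is slightly fewer chances to stop early and spare the boosters, the later surveys and the waitlist delivery of an ineffective programme.

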#### Trial status and review

The trial was reviewed and funded by Indian Council of Medical Research (Id: 2017–4697 version F1 dated 02 September 2019). The trial was reviewed and approved by the Institute Ethics Committee, NIMHANS (No.NIMHANS/19^th^IEC (BS&NS DIV.)/2019 on 2019-07-17. The trial was registered at Clinical Trials Registry-India with identification code: CTRI/2019/07/020394 dated 2019-07-29. Due to COVID-19 Pandemic and school closures, recruitment for the trial is anticipated after March 2022.

## Discussion

This pragmatic, cluster randomised waitlist-controlled design will examine the effectiveness of classroom-based teacher-led integrated school mental health intervention in improving school-going adolescent children’s mental health and well-being. To the best of our knowledge, this is the first study to integrate MHL with MHP and MH-FA for promoting mental health well-being among adolescent school children in India.

The trial is an extension of a series of focused research activities undertaken in Child and Adolescent Mental Health (CAMH) in Kolar district, Karnataka. The activities included situational analysis, numerous consultation workshops with teachers and various training programmes organised in-collaboration with the education department in Kolar. Following interactive discussions with NIMHANS experts and a national-level symposium, a road-map and draft action plan for integrated CAMH services in a district was finalised. The present trial is a part and extension of the action plan developed for promoting CAMH. Though the mental health intervention domains (MHP+ MHL + MH-FA) are closely interlinked with considerable cross-cutting areas of action, we intentionally compartmentalised it for better focus and delivery. With a need to build a more substantial evidence base on effective School Mental Health Promotion approaches in low-income countries, the study builds on the facilitating role of school climate in promoting mental health and related outcomes among adolescents and evaluates its effectiveness through a robust and systematic methodology.

### Limitations

As cultural aspects are likely to influence the effectiveness of SUMS interventions, the trial results should be interpreted within the given cultural context. As this study is being conducted in a relatively small geographical area, a larger multi-centre trial is required to better understand SUMS interventions’ replicability and scalability, especially in different cultural settings.

India has recently launched the Health and Wellness Ambassador initiative under the School Health Programme of Ayushman Bharat Mission [37]. This initiative trains two identified teachers from each school to facilitate the healthy survival of school children under 11 themes, including emotional well-being and mental health. In this context, the evidence obtained from this study will have implications for implementing and operationalising the Health and Wellness Ambassador initiative in schools. Further, the barriers and challenges identified in the present study will provide valuable inputs to improve school climate for promoting mental health among school-going adolescents, especially in resource-poor settings. This study will contribute significantly towards transforming the vision of shifting from “survival to healthy survival” of adolescent children in developing countries into reality.

## Data Availability

Data sharing is not applicable to this article as no datasets have yet been generated or analyzed.

## Abbreviations

CAMH: Child and Adolescent Mental Health
CD-RISC: Connor-Davidson Resilience Scale
DSMB: Data Safety & Monitoring Board
HPS: Health Promoting Schools
IASMHS: Inventory of Attitudes towards Seeking Mental Health Services
KII: Key informant interview
MH-FA: First Aid in Mental Health
MHL: Mental Health Literacy
MHLS: Mental Health Literacy Scale
MHP: Mental Health Promotion
MHPK: Mental Health Promoting Knowledge
NIMHANS: National Institute of Mental Health And Neuro Sciences
PMHSS: Peer Mental Health Stigmatization Scale
RE-AIM: Reach, Effectiveness, Adoption, Implementation, and Maintenance
RIBS: Reported and Intended Behaviour Scale
SUMS: Scaling Up of Mental health in Schools
TSC: Trial Steering Committee
